### Recruitment

The intention is to recruit 102 participants with distressing tinnitus and related insomnia from June 2017 to April 2019, which had been completed at the time of the proof-review of this article (November 2019). Participants will be identified from usual referral routes to the psychology service, where they will be informed of the trial as one option for care. To achieve adequate enrolment, the study will be advertised online via tinnitus charities, in print and web-based media outlets, across the hospital, and through regular briefings of local clinicians.

### Procedures

Participants responding to advertisements will complete basic eligibility screening with a clinical psychologist or research assistant using standardised measures of insomnia (ISI), tinnitus severity (Mini-TQ) and potential organic sleep disorders. If organic sleep disorder is indicated, a consultant in sleep medicine will manage queries, and onward referral will be advised as appropriate. If eligible, the GP will be informed and will have 3 weeks to ‘opt out’ of further care. Eligible individuals will be invited to attend a 1-hour full eligibility assessment with a clinical psychologist. Participants who are referred to the study by a clinician will complete eligibility criteria and the full assessment in the same appointment. If full eligibility is met, full informed consent will be collected by the clinical psychologist conducting the interview. The participants will receive sleep diary training and opt into Actiwatch (Philips Respironics, Murrysville, PA, USA) random allocation (one per group). They will be placed on a waiting list for randomisation, which will occur 3 weeks prior to intervention commencement. If eligibility is not met, alternative treatment or onward referral will be offered.

### Randomisation and blinding

Treatment will be group-based, with group sizes including six participants, on average. Treatment will be delivered in cohorts, with three groups, one for each arm of the study, running in parallel. Randomisation will be done using a customised computer algorithm for each cohort separately. The study requires individual randomisation with stratification for gender. Within each cohort, stratification will be used to ensure groups are comparable in gender composition. Because group size will be small per cohort, it was decided that stratification for age was not appropriate to run per cohort. Instead, age differences will be checked post-randomisation per group to ensure there are no significant group differences in age in each cohort.

Randomisation of consented participants will take place 3 weeks prior to the commencement of intervention. Age, gender and participant number will be provided to an independent party, who will use a computer-based random number sequence generation to allocate group. Allocation information will be returned to the research assistant, who will then notify participants of their group allocation (group 1, 2 or 3). Participants will only be informed of the treatment associated with their group number when they arrive at the first session. It is not possible to blind participants or therapists to allocation; however, participants will be blind to the content of the other therapies. Statistical analysis will be conducted by an independent statistician who will be blind to group (i.e., provided with group number, not group type).

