
### Additional measures

Baseline demographic and medical information will be reported: age, gender, ethnicity, marital status, education level, tinnitus duration, hearing loss, sleep, other audiological problems, other health problems and previous treatments. Previous research has indicated that sleep can change with age, so age will be included in the final model as a covariate.Use of psychotropic and hypnotic medications will be collected at each time point. If participants commence such medication, their results will be excluded from analysis. We will report numbers of any such changes across all groups.Use of night-time sound enrichment, naps, caffeine and alcohol will be collected at each time point because the offer of sound generators and advice regarding sleep hygiene is a systematic difference between treatment groups. We will report proportions of participants using night-time sound enrichment across groups, and we will also report proportions of patients showing reductions in caffeine, alcohol and naps across groups.One participant per treatment arm per cohort will be randomly allocated an Actiwatch to wear during the same time period as sleep diary completion. This will provide an objective comparator for the subjective diary data. This measure is limited because there is insufficient hardware available to include all participants.

Following treatment, participants will indicate the usefulness and relevance of treatment on 11-point Likert scales (0 to 10). They will be asked to provide qualitative feedback regarding their experiences and views of treatment.

A diagrammatic representation of the trial process (enrolment, intervention and assessment) is shown in the Standard Protocol Items: Recommendations for Interventions (SPIRIT) diagram (Fig. 2). For the full SPIRIT checklist, please see supplementary material Additional file 1.

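### Gender stratifies the randomisation and cohort blocks it, but the primary model as described names neither; the per-cohort age check should be descriptive only

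*Protocol article*

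**What the plan says.** Under Randomisation and blinding, the article runs three parallel groups per cohort, one per arm, and states: "Randomisation will be done using a customised computer algorithm for each cohort separately". Gender is the stratifier: "The study requires individual randomisation with stratification for gender". It is applied cohort by cohort: "Within each cohort, stratification will be used to ensure groups are comparable in gender composition". Stratifying by age was considered and rejected because the groups are small: "it was decided that stratification for age was not appropriate to run per cohort". In its place, "age differences will be checked post-randomisation per group to ensure there are no significant group differences in age in each cohort". No test, significance level or consequence is given.

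On the analysis side:

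- Additional measures notes that sleep changes with age, "so age will be included in the final model as a covariate".
- Primary outcome analysis specifies linear mixed models that allow for repeated measures and for the trial's clustering. It does not say whether the clusters are therapy groups, cohorts or both.
- Sample size describes clustering as six patients per group with a 7% within-group correlation.
- Sensitivity and other planned analyses compares results with and without adjustment for baseline characteristics, but only where these are imbalanced.

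**The concern.** An analysis should normally include the factors on which the randomisation was restricted. Stratification makes the arms alike on gender, and blocking makes them alike on cohort. A model that ignores these factors can leave the variation they explain in the error term, so intervals are wider than the design warrants.

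Here the stated rules point away from the design factors. Age, which was not stratified, is in the model. Gender, which was, is not named, and the only other route to adjustment depends on an imbalance that stratification is meant to prevent. Cohort matters more. Every cohort supplies one group to each arm, so a cohort effect cancels from the CBTi versus ABC difference. If the only cluster term is the therapy group, cohort variation still counts against that difference.

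The age check raises a separate question. Under correct randomisation any age difference is due to chance, and a covariate already deals with it. A check meant to secure a non-significant result either has no effect or, if acted on, changes an allocation already made.

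**Working it through.** **1. The plan's own figure.** Inputs from Sample size: effect size 0.8, 5% significance (two-sided assumed), 80% power, 10% loss, six per group, within-group correlation 0.07, correlation between measures 0.25.

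- Base: 2 × ((1.960 + 0.842)/0.8)² = 24.53 per group.
- Baseline-adjustment factor: 1 − 0.25² = 0.9375.
- Design effect: 1 + (6 − 1) × 0.07 = 1.35.
- Product: 24.53 × 0.9375 × 1.35 = 31.04.
- Loss: 31.04/0.9 = 34.49, or 31.04 × 1.1 = 34.15.

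This agrees with the stated 34. Neither gender nor cohort enters the calculation, so adding them to the model leaves N alone.

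**2. Gender.** The article gives no gender effect, so a range is assumed. With equal numbers of men and women and a gender effect of g SD, omitting gender raises the residual variance from 1 to 1 + g²/4. The standard error rises by the factor √(1 + g²/4) if errors are independent: 1.011, 1.031 and 1.077 for g = 0.3, 0.5 and 0.8.

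A simulation used six cohorts, 36 per arm in two arms, exact gender balance, independent errors, a true effect of 0.7 SD for power, and 4,000 runs per setting:

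| Assumed gender effect | Type I error, without / with gender | Power, without / with gender | Power lost (points) |
|---|---|---|---|
| 0.3 SD | 0.046 / 0.049 | 0.828 / 0.833 | 0.6 |
| 0.5 SD | 0.045 / 0.053 | 0.810 / 0.826 | 1.6 |
| 0.8 SD | 0.029 / 0.043 | 0.795 / 0.837 | 4.3 |

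Omitting gender makes the test conservative. The loss is small unless gender strongly predicts outcome.

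**3. Cohort.** Take the total variance as 1, with 0.07 between groups and 0.93 within. The variance of a group mean is 0.07 + 0.93/6 = 0.225. Suppose cohort adds a further c (assumed; the article gives none). A model with only a therapy-group term uses 0.225 + c where 0.225 is correct for the within-cohort contrast. The standard error ratio is √((0.225 + c)/0.225):

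- c = 0.02: √(0.245/0.225) = 1.04
- c = 0.05: √(0.275/0.225) = 1.11
- c = 0.10: √(0.325/0.225) = 1.20

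**4. What fixed cohort effects cost.** 102/18 = 5.7, so about six cohorts and 18 groups. Group-level degrees of freedom are 18 − 3 = 15 without cohort and 15 − 5 = 10 with it. The critical t rises from 2.13 to 2.23, about 4.5%. Net interval width with cohort relative to without is 1.045/1.04 ≈ 1.00, 1.045/1.11 ≈ 0.94–0.95 and 1.045/1.20 ≈ 0.87. Fixed cohort effects therefore break even near c = 0.02 and gain above it.

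**5. The age check.** Assume one three-group test per cohort at 5%.

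- Chance of at least one flag under correct randomisation: 1 − 0.95⁶ = 26% for six cohorts; 1 − 0.95⁵ = 23% for five.
- Power of a one-way analysis of variance with six per group (simulated) when one arm is shifted in age: about 24% for 0.8 SD and 34% for 1.0 SD.

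**The case against.** The strongest reply is that silence is not exclusion. The sentence on age explains why age is included; it does not close the list of covariates. A journal article condenses the model, and the full specification is commonly left to an analysis plan that is not shown. This stands in part: nothing says gender is excluded, and the clustering the model allows for may already include cohort, in which case the cohort loss is nil. But the article does go beyond silence. It names one covariate for the final model and sends other baseline adjustment to an imbalance-triggered sensitivity analysis. Taken together, those rules leave the stratifier out.

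A second reply is that the cohort figures rest on assumed shares. The 7% comes from an uncontrolled evaluation of group CBTi, where cohort and group variation could not be separated, so some cohort variation may already sit inside the 7% and the sample size would have allowed for it. That is fair. The figures are a range under stated assumptions, not estimates.

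Three stronger readings are tempting but not supported:

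- **That the age check replaces the age covariate.** The contrast drawn under Randomisation and blinding is with stratifying by age. Additional measures keeps age in the model, so both apply.
- **That the check interferes with allocation.** No reallocation is stated. The wording leaves the consequence open.
- **That the treatment estimate is biased, the sample size wrong or the stratification wasted.** Stratification still delivers comparable gender composition whatever the model, and the effect is on precision only.

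**Conclusion.** The point holds as a modest matter of precision and clarity. As described, the primary model does not carry the stratification factor and does not say whether it carries the block. The result would be standard errors that are somewhat too large and tests that are mildly conservative, with no bias and no change to 34 per group.

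The gender part is minor: about 0.6 to 4.3 power points for assumed gender effects of 0.3 to 0.8 SD with independent errors. The cohort part ranges from nothing, if cohort is already modelled, to about 4%, 11% or 20% on the standard error for assumed extra variance of 2%, 5% or 10%.

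The age check is uninformative under correct randomisation, and its consequence is undefined. The 26% false-alarm figure assumes six cohorts, independent tests and a 5% level that the article does not state.

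**What to change.** State the primary linear mixed model as follows: gender as a fixed effect, cohort as a fixed or random effect, therapy group (arm within cohort) as a random effect, repeated measures within participant, and age as already planned. Do not make gender or cohort adjustment depend on observed imbalance. The cost is a sentence or two of wording, one degree of freedom for gender, and about five group-level degrees of freedom if cohort is fixed. Because fixed cohort effects only break even when cohort variation is small, choose between fixed and random before the outcome data are examined by arm.

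Describe the age comparison as descriptive and rely on the age covariate for chance imbalance. The Recruitment section says recruitment had finished by proof review, so removing the check would now change little. The useful step is to report whether any cohort's allocation was ever redrawn or altered because of it. If one was, the randomisation should be described accordingly. If none was, one sentence settles the matter.

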### Intervention

All interventions will take place in the same place, on the same day, at different times. The same two clinical psychologists will conduct all treatments together. They both have significant experience, skills and knowledge of working with chronic tinnitus, insomnia, group therapy, supportive interventions and CBTi. Treatment sessions will be 120 minutes in duration, and follow-up sessions will be 90 minutes in duration. There are three intervention options:
**Audiology-based care (ABC):** ABC will be based on the best care currently available to patients with tinnitus and insomnia in the United Kingdom. There is no set standard, so this group has been designed to capture what is currently seen as best advice for people with tinnitus and insomnia. The group has been designed to be as effective as possible, because the intervention is being delivered by two clinical psychologists experienced in working in an audiological setting and in a supportive group setting. Intervention includes information and psychoeducation about tinnitus, sleep and relaxation. A bedside sound generator will be on loan for 3 months. Therapeutic contact is limited to two sessions 8 weeks apart. Supporting literature (leaflets from the British Tinnitus Association on sleep, tinnitus and relaxation) will be provided.**Cognitive behavioural therapy for insomnia (CBTi):** CBTi will follow the UK standard treatment of primary insomnia, adapted for tinnitus. This multi-component treatment includes time-in-bed restriction, stimulus control, sleep hygiene, relaxation, paradoxical intention, cognitive restructuring, behavioural experiments and behavioural activity change. Additional discussions will focus on information, psychoeducation and advice about tinnitus management. Six sessions will occur over 8 weeks (four weekly sessions followed by two fortnightly sessions).**Sleep support group (SSG):** This supportive intervention focuses on the benefits of clinical contact and a supportive milieu. It is an active condition controlling for the non-specific benefits of supportive group therapy. Sleep and tinnitus will be discussed from a personal perspective, focusing on personal stories and how participants cope. Participants will be encouraged to support each other. No expert audiological or psychological information will be provided, but therapists will facilitate discussion and adaptive group dynamics. Six sessions will follow the pattern of CBTi (four weekly sessions followed by two fortnightly sessions).

### Treatment fidelity

Treatment fidelity will be assessed by a clinical psychologist not involved in treatment. A random selection of treatment sessions will be recorded and assessed using a fidelity checklist. The two treating clinicians will discuss each session to assess fidelity independently of this, and breaches will be reported.

## Assessments and outcomes

### Timing of assessments

Participants will be recruited from August 2017 to April 2019, which had been completed at the time of proof-review of this article (November 2019). Screening will be followed by full psychological assessment. Outcome measures will be reported at baseline (3 weeks post-randomisation) and at 10 weeks (post-treatment), 14 weeks (1 month follow-up) and 34 weeks (6-month follow-up) post-randomisation. Figure 1 shows the Consolidated Standards of Reporting Trials (CONSORT) flow diagram for the study.

**Fig. 1 Fig1:**
[figure not shown]
CONSORT flow diagram

### Managing loss to follow-up

The rationale for the repeated measures will be indicated to encourage follow-up. Completed measures will be checked so that missing items can be minimised. Participants who do not attend all sessions will be contacted and asked to complete and return outcome measures. Participants who request to end participation in the trial will be invited to an individual follow-up session and offered further treatment outside of the trial if required.

### Screening measures

Three screening measures will be used:
Total score of the ISI patient version [36]. This seven-item self-report questionnaire assesses the severity, impact and characteristics of insomnia over the last 2 weeks. A 5-point Likert scale (from 0 = no problem to 4 = very severe problem) yields a total score ranging from 0 to 28, with scores of 15–21 reflecting moderate insomnia and higher scores reflecting severe insomnia. A minimum score of 15 (moderate insomnia) is required to meet eligibility criteria.Total score on the Mini-TQ [37], a psychometrically approved brief tool for effective assessment of tinnitus-related distress. A minimum score of 8 (moderate distress) is required to meet eligibility criteria.Sleep Disorder and Scoring Proforma, a clinical tool used routinely in the hospital, includes a list of common symptoms indicative of organic sleep disorders. Occurrence of symptoms will be discussed with a consultant in sleep medicine, and only those not requiring further sleep investigations will be included.

### Outcome measures

The primary outcome will be reduction of insomnia (ISI) and improvement in subjective sleep (diary) from 3 to 10 weeks, 14 weeks and 34 weeks post-randomisation. Daily sleep diaries will be completed by participants at home; questionnaire data will be completed independently in the treatment session and collected by the trial therapists.
ISI has excellent internal consistency in patient samples (Cronbach’s α 0.91), is sensitive to treatment response and can show the clinical significance of change (whilst sleep diaries are limited to showing statistical significance) [33]. The ISI will be treated as a continuous variable, and groups will be compared on mean ISI change score from pre- to post-treatment and to follow-up. They will also be compared on the proportion of individuals showing change at the minimally important difference level, which is a reduction of at least 6 points [38]. Sleep diaries will allow calculation of the continuous variables SE (percentage of time in bed spent asleep), TST, and total wake time (TWT) over 2 weeks. Calculations will offer weekly mean averages and nightly variability measures.Secondary outcome measures will include additional measures of sleep, tinnitus, psychological distress and functioning, and all will be treated as continuous outcomes based on the mean or the total score (defined below). The Pittsburgh Sleep Quality Index [39] provides a global picture of severity of sleep problems by accounting for quantitative and qualitative dimensions. It has shown high sensitivity and specificity in distinguishing good and poor sleepers in samples of medical and psychiatric patients. It produces seven component scores summed to produce the global index score (0–21), with higher scores indicating lower quality and a score > 5 indicating ‘poor sleep’.The Dysfunctional Beliefs and Attitudes About Sleep Questionnaire–abbreviated version (DBAS-16) [40] is a self-report questionnaire designed to identify unhelpful sleep-related beliefs that are presumed to perpetuate insomnia and to assess changes in those beliefs that result from CBTi. There are 16 statements about sleep, to each of which participants are asked to agree/disagree on a 10-point Likert scale, and the mean score based on all 16 items is calculated. The DBAS-16 has good psychometric properties (α = 0.8).The Tinnitus Questionnaire (TQ) [41] will be used as our outcome measure for tinnitus distress. It is a self-report questionnaire with 41 items that contribute to a total score on five sub-scales (emotional disturbance, intrusiveness, auditory perceptual difficulties, sleep disturbance and somatic complaints). Items are scored 0–2, with total or sub-scale scores calculated [41]. There is high test-retest reliability (*r* = 0.94) and internal consistency (α = 0.93) [42]. In addition to comparison of change in total TQ score across groups, the TQ will be categorised to indicate the number of individuals who show reliable change from pre- to post-treatment and to 6-month follow-up. Reliable change on the TQ is indicated by a reduction of at least 11 points [16].The Tinnitus Catastrophizing Scale (TCS) [43] assesses negative cognitions about tinnitus on a 13-item scale, which has shown good internal consistency. The total score of the TCS will be analysed as a continuous variable.Subjective tinnitus loudness will be measured as a continuous variable using a visual analogue scale (VAS).Psychological distress will be assessed using the 34-item Clinical Outcomes in Routine Evaluation–Outcome Measure (CORE-OM) [44]. This pan-diagnostic measure of general psychological distress assesses well-being, symptoms, functioning and risk with 34 items rated on a 5-point scale (0 to 4). Internal reliability of the CORE-OM domains is appropriate (ranging from α > 0.75 to < 0.95). Convergent validation against other measures and clinician ratings is good [45]. Groups will be compared on change in the CORE-OM clinical score (calculated as the mean score, multiplied by 10). CORE-OM clinical score will also be used to categorise individuals as those who show reliable change from pre- to post-treatment and to 6-month follow-up (a reduction of 5 points or more) [16].The Patient Health Questionnaire-9 (PHQ9) will assess depressive symptoms on nine items rated on a 0 to 3 scale, where a score of 10 or more equates to clinically significant symptoms [46]. Groups will be compared on change in total score.The Generalized Anxiety Disorder Assessment-7 (GAD-7) will assess anxiety symptoms on seven items rated on a 0 to 3 scale, where a score of 8 or more demonstrates clinically significant symptoms [47]. Groups will be compared on change in total score.The Work and Social Adjustment Scale (WSAS) [48] measures general functioning in terms of impairments related to tinnitus measured on five items rated on a 0 to 8 scale, where a score of 10 or more indicates clinical significance. Groups will be compared on change in total score.The widely used EuroQoL (EQ-5D) [49] will measure health-related quality of life. Five questions assessing different dimensions (mobility, self-care, usual activities, pain/discomfort and anxiety/depression). The answers are converted into EQ-5D index and utility scores anchored at 0 for death and 1 for perfect health. A VAS reports on subjective health status from 0 (worst) to 100 (best). Groups will be compared on mean change in index score and VAS.Change in mean scores on subjective measures from 2-week sleep diaries (rated as 0–10) will be compared between groups, including nightly rated sleep quality, tinnitus annoyance (0 to 10) and daily rated daytime functioning.

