### Sample size

We calculated the sample size required to test the primary hypothesis on the basis of a recent meta-analysis of 14 randomised controlled trials comparing CBTi with control groups in the treatment of primary insomnia [22]. Here, between-group comparisons reported effect sizes on subjective sleep variables (Cohen’s *d*) as ranging from medium (*d* = 0.44) to large (*d* = 1.09) across a range of control groups (including no intervention, placebo control, waiting list, treatment as usual and information controls). Similarly, medium to large effect sizes were seen on self-rating measures. When looking at treating insomnia in the context of a chronic health condition such as pain, similar moderate to large effect sizes are reported [27]. These findings have led us to base a power analysis on an assumed effect size of 0.8.

Estimation of potential loss to follow-up was set at 10%, based on rates reported by Okajima et al. [22], as ranging from 0% to 33% and as 8% from a clinical evaluation of CBTi within a tinnitus clinic [31]. We assumed a cluster design with six patients per group, and we assumed a within-group correlation of 7%, estimated from a previous study [31]. Correlation between measures was estimated as 25% on the basis of a small pilot study. It is likely that the true correlation will be higher, so this estimate has a conservative effect on required sample size. Assuming a significance level of 5% and 80% power, the number of participants needed to detect a statistically significant difference between the CBTi and ABC groups on the primary measures of interest was 34 per group (102 across all three groups).

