### Sensitivity and other planned analyses

Additional sensitivity analysis will be conducted as follows: outliers (analyses with and without outliers), non-compliance (a per-protocol analysis), baseline imbalance (analyses with and without adjustment for baseline characteristics, if imbalanced), and impact of distributional assumptions (analysis plan will assume a normal distribution for continuous outcomes, and this will be tested for goodness of fit in the analysis). In addition, sensitivity analyses will be conducted using other suitable distribution under further statistical advice.

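### The primary comparison is worded as mean change with no baseline score prespecified as a covariate, whereas 34 per arm fits a baseline-adjusted analysis when all stated inputs are used

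*Protocol article*

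**What the plan says.** The research hypotheses and the Outcome measures section of the protocol article frame the primary outcomes (ISI, and SE and TST from the diary) as changes from the week-3 assessment. For the ISI, "groups will be compared on mean ISI change score from pre- to post-treatment and to follow-up".

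The Primary outcome analysis section specifies linear mixed models that allow for repeated measures and for clustering. It does not say whether the baseline score enters as a covariate, as a response with means constrained equal, or as an unconstrained response. Under Additional measures, "age will be included in the final model as a covariate"; no other covariate is named. Baseline adjustment appears only among the sensitivity analyses: "baseline imbalance (analyses with and without adjustment for baseline characteristics, if imbalanced").

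The Sample size section states: "These findings have led us to base a power analysis on an assumed effect size of 0.8". It sets 10% loss, six patients per group, a within-group correlation of 7%, a 5% significance level and 80% power. It adds: "Correlation between measures was estimated as 25% on the basis of a small pilot study". It says the true correlation is probably higher, which would lower the number needed. The result is 34 per arm for CBTi against ABC, 102 in all. Neither the formula nor the SD that standardises d is given.

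**The concern.** A correlation between repeated measures enters a two-arm calculation differently according to the analysis. Relative to the variance of a single post-treatment score, the factor is 1 − ρ² for a baseline-adjusted comparison and 2(1 − ρ) for a raw pre-post change. At ρ = 0.25 these are 0.9375 and 1.5, so the raw change contrast carries only 0.9375/1.5 = 62.5% of the information of the adjusted one.

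The text describes the comparison as change and leaves baseline adjustment to a conditional sensitivity analysis. If the primary model is carried out as a plain change contrast, the planned power may not belong to the analysis that is run. Making adjustment depend on observed imbalance also lets the data decide whether the more precise analysis is reported. Recruitment had ended by the time of the article's proof review, so the model is the remaining way to protect precision.

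**Working it through.** **Inputs** (Sample size section): d = 0.8; α = 0.05, taken as two-sided because sidedness is not stated; power 0.80; m = 6 per group; ICC = 0.07; ρ = 0.25; loss 10%; 34 per arm. Equal variances at all times are assumed.

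**Common quantities**
- Unadjusted n per arm: 2(1.96 + 0.8416)²/0.8² = 24.53.
- Design effect: 1 + (6 − 1) × 0.07 = 1.35.
- Retained per arm: 34 × 0.9 = 30.6.

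**Reproducing the stated 34, with all inputs used**
- Baseline-adjusted: 24.53 × 0.9375 × 1.35 = 31.04. Inflated for loss, × 1.1 = 34.1 and /0.9 = 34.5. Strictly these round up to 35, so the match is approximate.
- Power with 30.6 per arm: SE = √(2 × 0.9375 × 1.35/30.6) = 0.288; 0.8/0.288 = 2.78; power 79%.

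**Plain pre-post change, same inputs, d in raw-score SD units**
- Design effect applied to the whole change variance: 24.53 × 1.5 × 1.35/0.9 = 55.2, so 55 to 56 per arm. SE = √(2 × 1.5 × 1.35/30.6) = 0.364; 0.8/0.364 = 2.20; power 59%.
- Clustering on the post score only, since baseline precedes therapy: variance factor 1.5 + 0.35 = 1.85; 24.53 × 1.85/0.9 = 50.4 per arm; SE = √(2 × 1.85/30.6) = 0.348; power 63%.

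**Other readings of the change comparison**
- d in change-score SD units: factor 1, so 24.53 × 1.35/0.9 = 36.8 per arm. Power with 30.6 retained is 77% (81% with no loss).
- Change to the mean of weeks 10, 14 and 34 at ρ = 0.25: factor (1 + 2ρ)/3 + 1 − 2ρ = 0.5 + 0.5 = 1.0, so the same 77%.

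**Dependence on ρ** (30.6 retained per arm, design effect 1.35, raw-score SD units)

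| ρ | Change, power | Baseline-adjusted, power |
|---|---|---|
| 0.25 | 59% | 79% |
| 0.4 | 69% | 84% |
| 0.5 | 77% | 87% |
| 0.6 | 85% | 92% |

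The change contrast equals the planned precision when 2(1 − ρ) = 0.9375, that is ρ = 0.53. At any one ρ, 2(1 − ρ) − (1 − ρ²) = (1 − ρ)², which is positive for every ρ below 1, so adjustment is always the more precise.

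**Few clusters.** 34/6 is about six therapy groups per arm. If the test used 10 to 15 degrees of freedom (an illustrative assumption), adjusted power by the noncentral t would be 71% to 74% rather than 79%.

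**The case against.** A reader might infer that 34 per arm can come only from a baseline-adjusted formula. The documents do not support that. 24.53 × 1.35 = 33.1, which rounds up to 34 with no adjustment if loss and correlation are both left out. Applying the design effect to the 5.4 patients retained per group gives 36 with loss and no correlation, which is also near. Against these routes, the Sample size section presents both the loss rate and the correlation as inputs, and the adjusted route is the one that uses them all and lands close to 34. That makes it the best fit; it does not prove it was the method used.

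A reader might also infer that the plan leaves the baseline score out of its primary model and therefore has 59% power. The protocol never says so. A repeated-measures mixed model can have the precision of covariate adjustment, depending on how baseline enters. Comparing mean change with baseline as a covariate gives the same treatment effect and standard error as adjusting the post score. Naming age does not exclude other covariates, and an analysis plan that is not shown may settle the matter. All of this stands, and it makes 59% conditional. The lower figure also depends on a single post time point and on d in raw-score SD units; the other readings give 63% to 77% after loss.

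The article expects a correlation above 0.25, and at 0.6 a change contrast would reach 85%. That helps only from about 0.53, more than twice the pilot value, and the adjusted analysis gains from it too.

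What the objection leaves untouched is that the only treatment of baseline the text fixes is the less favourable one: a change comparison, with adjustment confined to a check triggered by imbalance.

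**Conclusion.** The concern holds as a mismatch in specification with a free improvement available. It is not a demonstrated loss of power. The wording of the primary comparison and the basis of the sample size are not shown to agree. Using all stated inputs, 34 per arm is approximately what a baseline-adjusted analysis needs (34.1 to 34.5, 79% power). A plain change contrast at ρ = 0.25 would have about 59% to 63% power and need about 50 to 56 per arm, if d is in raw-score SD units and one post time point is used. It would have about 77% if d is in change-score SD units or if the three follow-ups are averaged. None of the change-score readings examined reaches 80% after the planned loss at that correlation.

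These figures assume a two-sided test, equal variances and a normal approximation. The 71% to 74% figure rests on assumed degrees of freedom and is an illustration only.

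**What to change.** - In the primary mixed model for ISI, SE and TST, prespecify the baseline value of the same measure as a covariate with weeks 10, 14 and 34 as outcomes, or keep baseline as a response with means constrained equal across arms.
- Report adjusted mean differences between arms in place of raw differences in change.
- Remove the imbalance condition for baseline outcome scores. It may remain for other characteristics as a sensitivity analysis.
- In the Sample size section, state which SD standardises d and how the correlation and the loss enter. Say that the 80% refers to the baseline-adjusted analysis under a normal approximation, and that it is somewhat lower with small-sample degrees of freedom for about six therapy groups per arm.

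The cost is model wording and a slightly more modest power statement. The baseline scores are already collected, and enrolment does not change.
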